### Randomization to treatment groups

Separate randomization files will be created for each of the two sites. The random group assignments will be based on a block design where the block size is not constant.

At the end of each baseline interview, participants will be randomly assigned by computer to an acupuncture treatment or to continued access to usual care. At the time of randomization, the computer informs the Research Specialist and participant of assignment to an acupuncture treatment or to usual care. The specific acupuncture treatments participants are assigned to are only revealed to the treating acupuncturist, immediately prior to treatment. The random assignments cannot be viewed in advance and cannot be changed after randomization.

### Study treatments

In the three acupoint stimulation groups, participants will be treated twice weekly for the first three weeks, and then weekly for four weeks (a total of 10 treatments over seven weeks). Ten treatments were chosen because over 75% of the acupuncturists we surveyed believed 8 treatments would be necessary to treat chronic back pain [19]. These treatments will be provided at no cost to study participants. Electrostimulation, moxibustion, herbs, and other non-needle treatments and adjuncts will not be allowed in this trial.

All participants will be mailed the Back Pain Helpbook[20]within a week of randomization. This evidence-based manual for self-management of chronic back pain includes information on managing flare-ups, physical activity and exercise, and appropriate life-style modifications. From a practical viewpoint, we thought that giving this book to participants in the usual care group would minimize their disappointment at not receiving acupuncture treatment and would therefore reduce losses to follow-up. From a scientific viewpoint, providing the back-care book to all participants permits assessment of the efficacy of acupuncture beyond educational materials alone.

In our pilot study, we found that we could successfully mask participants to treatment group by using two acupuncturists who have minimal contact with each other: a "Diagnostician acupuncturist" who prescribes an individualized treatment plan at each visit and a "Therapist acupuncturist" who provides the treatment to which the participant was randomized. The Diagnostician acupuncturist will evaluate the participant at each visit using TCM diagnostic techniques and will then write a prescription for an individualized treatment designed to treat the back pain and any underlying TCM "constitutional deficiencies" that could prevent the pain from resolving or give rise to recurrences. A Research Specialist will then accompany the participant from the Diagnostician acupuncturist to the Therapist acupuncturist who will then administer the randomly assigned treatment, interacting minimally with the participant. Only one-third of participants randomized to an acupuncture treatment will actually receive the individualized treatment.

#### a) Individualized acupoint stimulation treatment

In this arm, the Therapist will administer the treatment prescribed at the beginning of each visit by the Diagnostician. This treatment may include acupoints on any part of the body that can be needled while the participant is lying prone with his/her head in a face cradle. There are no constraints on number of needles, depth of insertion, or needle manipulation. This arm of the trial resembles clinical practice where patients receive customized treatments that may vary from visit to visit.

#### b) Standardized acupoint stimulation treatment

We previously developed a standardized needling prescription (Table 2) considered effective for chronic low back pain [18]. All acupoints will be needled with sterile disposable 32-gauge needles (0.25-mm) for 20 minutes, with stimulation at 10 minutes and again just prior to needle removal. A 1.5-inch needle will be used for most acupoints, but longer needles will be used for acupoints where deeper needling is appropriate. Needles will be inserted to the depth typically recommended for that acupoint, generally between 1 and 3 cm [21]. Because 90% of the acupuncturists we surveyed felt that the phenomenon of *de qi *was important to successful treatment of back pain [19] it is an integral part of our treatment protocol. *De qi *is usually described by the patient as a feeling of numbness, heaviness or distention at the needle site [22]. However, there is also a biomechanical component to *de qi *that is felt by the practitioner. This "needle grasp response" occurs when tissue tightens around the inserted needle and constricts its movement [23], and is poetically described in the ancient texts as "the feeling of a fish biting on a fishing line" [24]. Therapists will detect *de qi *using the needle grasp response thereby avoiding discussion of the needling sensation with the patient and maintaining masking of the participant to treatment to the greatest extent possible. This approach will also be used in the individualized treatment.

**Table 2 T2:** Standardized acupoint stimulation treatment

**Acupoints**	**Location**	**Major Indications and Actions**. [21,38]
Du3 (Yaoyang-guan)	Midline of the lower back, just below the spinous process of the fourth lumbar vertebra	Lumbosacral pain, motor impairment, numbness and pain of legs, other (e.g., seizures)
UB23 (Shenshu)	1.5 inches lateral to lower border of the spinous process of the second lumbar vertebra (bilateral point)	Low back pain, principal point to strengthen the "Kidneys", other (e.g., weakness of knee)
Low back ashi	Any tender point in the area between a horizontal line just below T12 and a horizontal line at the tip of the coccyx and extending to the outer contour of the body (as assessed by the Diagnostician acupuncturist)	Used according to the concept that "where there is pain, there is an acupuncture point"
UB40 (Weizhong)	Back of the knee in the midpoint of the transverse crease of the popliteal fossa (bilateral point)	Low back pain, motor impairment of hip joint, "activation of the UB channel"
Ki3 (Taixi)	On the foot, depression between the medial malleolus and tendo calcaneus (bilateral point)	Lumbar pain, strengthen lumbar spine, "nourishes Kidney Yin and tonifies Kidney Yang", other (e.g., insomnia)

#### c) Non-insertive acupoint stimulation treatment (simulated acupuncture)

We previously developed and tested a simulated acupuncture technique using a toothpick in a guidetube and determined that the technique was considered a credible acupuncture treatment by participants with low back pain [25] The acupuncturist will simulate insertion of needles, using the toothpick and guidetube technique, at the same eight acupoints used in the standardized treatment (Du3, UB23-bilateral, low back ashi, UB40-bilateral, Ki3-bilateral). Simulating insertion involves holding the skin taut around each acupoint and placing a standard acupuncture needle guidetube that contains a toothpick against the skin. The acupuncturist then taps the toothpick gently, twisting it slightly so that it feels to the participant like an acupuncture needle grabbing the skin, and then quickly withdraws both the toothpick and guidetube while keeping his or her fingers against the skin for a few additional seconds to imitate the process of inserting the needle to the proper depth. All acupoints will be "stimulated" with toothpicks at 10 minutes (i.e., the acupuncturist will touch each acupoint with the tip of a toothpick without the guidetube, rotate the toothpick clockwise and then counterclockwise less than 30 degrees) and again at 20 minutes just before they are "removed." Location of the correct acupoints for initial and subsequent stimulation will be facilitated by having marked all the acupoints with non-toxic ink prior to initiation of treatment. To simulate withdrawal of the needle, the acupuncturist tightly stretches the skin around each acupoint, presses a cotton ball firmly on the stretched skin, then momentarily touches the skin with a toothpick (without the guidetube) and quickly pulls the toothpick away using the same hand movements as in regular needle withdrawal. For verisimilitude, the Therapists will crinkle an empty needle wrapper to simulate the sound of unwrapping needles before treatment and will flick the side of the Sharps container after needle withdrawal to simulate the sound of needle disposal.

#### d) Usual care

We have included a usual care treatment arm to permit us to determine if individualized or standardized acupuncture offers advantages over standard care for chronic low back pain. Members of this group (as well as members of the three acupuncture treatment groups) will continue to receive the medical care they would have received in the absence of the study. This typically involves continued use of medications (mostly non-steroidal anti-inflammatory medicines), and occasionally, provider visits.

### Clinic sites

Acupuncture treatments will be performed in the Research Clinics at the two study sites. The Diagnosticians and Therapists will see participants in separate rooms. Therapists' rooms will resemble a typical acupuncture treatment room with a massage table for treatment and a table for acupuncture supplies. This table will be screened off from the massage table to prevent participants from looking at the needles or non-insertive implements to be used in their treatment.

### Study acupuncturists

Licensed acupuncturists will be recruited and trained as either Diagnosticians or Therapists and will function only in their assigned role throughout the study. All acupuncturists will be experienced TCM practitioners. We will require Diagnostician acupuncturists to have at least five years experience and Therapists to have at least three years experience with an emphasis on the treatment of musculoskeletal pain. All acupuncturists will need to agree to strictly adhere to the study protocol and to complete the rigorous training program developed in the pilot study. In addition, the Therapist acupuncturists will need to be comfortable administering all three treatments.

### Training and monitoring of acupuncturists and clinic staff

Prior to beginning the study, Acupuncturist Diagnosticians, Acupuncturist Therapists and Research Assistants will undergo intensive and customized training in the clinical protocol. There will be "dress rehearsals" with scripted "participants" to ensure that the clinical treatment team is able to adhere to the protocol under a variety of challenging participant scenarios. Much of the communication between the Therapists and the participants and between the Research Assistants and the participants is scripted and we have standard answers to commonly asked questions. The Research Assistants will use a special clinic visit form to document deviations from protocol by themselves or by the acupuncturists. Site visits will occur about 4 and 16 months after treatment begins to ensure continued adherence to study procedures.

### Assessment of outcomes

A core set of recommended outcome measures [26] covering five important domains will be assessed: back-related dysfunction, pain, general health status, disability and patient satisfaction. The primary efficacy/effectiveness outcomes are pain and dysfunction. There will be no physical assessments or laboratory tests because these have not been found to be useful for assessments of outcomes in studies of mechanical back pain. The primary assessment will be the 8-week telephone interview.

Table 3 below summarizes the categories of questions that are included in the baseline and follow-up questionnaires.

**Table 3 T3:** Content of baseline and follow-up questionnaires

**Measures**	**Baseline**	**8-Week**	**26-Week**	**52-Week**
Sociodemographic characteristics	x			
Back pain history	x			
* **Roland Disability Questionnaire (dysfunction)**	x	x	x	x
* **Bothersomeness of low back pain**	x	x	x	x
Satisfaction with back care	x	x		x
General Health Status (SF-36)	x	x		x
Disability days	x	x	x	x
Medication use	x	x	x	x
Worry about back problem	x	x	x	x
Exercise (Back-related, general)	x	x		x
Confidence in ability to self-manage future back pain	x	x		x
Expectations of treatment	x			
Knowledge of acupuncture	x			
Adverse experiences		x		
Perceptions of acupuncture experience (acupoint stimulation participants only)		x		
Perceptions of book on self-care		x		x
Use of non-HMO services for back pain		x	x	x

Use and cost of HMO services for back pain [from automated HMO databases]

* Co-primary outcome measures

### Primary measures of efficacy/effectiveness

The modified Roland-Morris Disability Questionnaire will be used to measure back-related patient dysfunction [26,27]. This instrument, which asks 23 yes/no questions, takes approximately five minutes to complete. A composite score is obtained by summing up the number of "yes" responses, so the total scores range from 0 to 23. It has been found to be reliable, valid and sensitive to clinical changes [27-32] and is well suited for telephone administration.

Because there are individuals who are very bothered by even a small amount of pain and others who are not bothered by even moderate pain, our primary measure of symptoms assesses participants' perceptions of the impact of pain on their lives rather merely assigning a pain severity score. Thus, participants will be asked to rate how bothersome their low back pain has been during the past week on a 0 to 10 scale where 0 represents "not at all bothersome" and 10 "extremely bothersome". This measure appears to have substantial construct validity – i.e., it is highly correlated with measures of function and other outcome measures [27].

Both primary outcomes will be measured at baseline and during the 8, 26 and 52 week follow-up interviews. The trial's primary endpoint will be the 8 week follow-up, one week after completion of the 10 acupuncture treatments. All interviews will be conducted using computer-assisted telephone interviews (CATI).

### Secondary measures of efficacy/effectiveness

General health status will be measured using the well-validated SF- 36 [33] that has been recommended for use in studies of back pain [26,34]. The SF-36 measures eight health concepts: 1) limitations in physical activities because of health problems; 2) limitations in social activities because of physical or emotional problems; 3) limitations in usual role activities because of physical health problems; 4) bodily pain; 5) general mental health (psychological distress and well-being); 6) limitations in usual role activities because of emotional problems; 7) vitality (energy and fatigue); and 8) general health perceptions.

Satisfaction with information given about the cause of the back problem, treatments received, and overall care will be measured using three separate questions, each with a 5-point Likert scale (ranging from very satisfied to very dissatisfied). Days of restricted activity due to back problems, a surrogate for disability, will be measured with a back-pain specific modification of 3 National Health Interview Survey questions about the number of half-days spent in bed, home from work or school, or cutting down on usual activities due to illness or injury during the past week [35].

Efficacy will be determined by comparing outcomes among the four treatments arms, adjusting for baseline values. The analytic plan is described below.

### Measures of health care resource use

Participants' use of health care for back pain during the year following randomization will be determined from automated utilization data, interview data on out-of-plan utilization, and records for each visit to the study acupuncturists. The automated utilization data provide complete information about all provider visits and hospitalizations at health plan facilities or paid for by the health plan. Visits for back pain can be identified by the diagnosis listed for every visit and hospitalization. Imaging of the lower back can also be identified by specific procedure codes. Our previous studies have found that the automated data are as reliable as chart data for identifying provider visits and imaging for back pain, but much less costly.

Visits to non-study acupuncturists and providers not covered by the health plan will be estimated from the interview data for the time period since the previous interview. In other words, the 8-week interview will request information about out-of-plan utilization since participants were randomized to study treatment, the 26-week interview will ask about the previous 18 weeks, and so forth. To increase the accuracy of response, we will mail participants Health Care Utilization logs to track visits they make for their back pain shortly after randomization and after 8 and 26 weeks. This will permit determination of the percentage of participants in each treatment group who had any visits for low back pain during and following the intervention period, as well as estimation of the mean number of visits. Current use of medications of all types for low back pain will be captured in the follow-up interviews.

Costs of back-related care will be estimated by assigning dollar values to each service. Costs of specific services (e.g., visits, imaging studies, medications) will be determined using data from both sites' cost management information systems which define cost based on standard relative value units (RVUs) assigned to actual department RVUs produced. Costs of the acupuncture interventions will be distinguished from the costs of all other back pain-related services to permit separate comparisons among the treatment groups of the costs of the interventions themselves, of the non-intervention back care costs during the 7-week treatment period, and of the total back pain-related costs incurred over the 45 week period between completion of the study interventions and the end of the 52 week follow-up period.

## Protection of human subjects and assessment of safety

### Protection of human subjects

This study protocol was approved by the Institutional Review Boards of Group Health Cooperative and Kaiser Foundation Research Institute.

### Data safety monitoring board

The Data Safety Monitoring Board (DSMB) established by the National Center for Complementary and Alternative Medicine to monitor large trials will monitor the progress of the trial and review safety data.

### Adverse events

Participants will be asked about adverse experiences at each clinic visit and during the 8-week telephone interviews. We will define an adverse experience as any unfavorable and unintended sign, symptom or disease temporally associated with the use of the acupuncture treatments, which could reasonably be related to the procedure. Because acupuncture has relatively short-term physiological effects, we will not report adverse events that first manifest more than two weeks after a participant's final acupuncture treatment (or more than 9 weeks after randomization for the usual care control group). Any adverse event that is life-threatening or results in death, hospitalization, a persistent or significant disability/incapacity, a congenital anomaly/birth defect, or cancer will be promptly reported to the DSMB.

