## Methods and design

### Overview

Eligible participants at two sites will be randomized equally to one of four treatments: individualized acupuncture point stimulation, standardized acupuncture point stimulation, non-insertive simulated acupuncture point stimulation, or usual care (Figure 1). Participants in all three "acupuncture" arms will receive 10 "treatments" involving stimulation of acupuncture points over a 7-week treatment period (two treatments per week for 3 weeks, weekly treatments for 4 weeks).

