## Stopping rules

The trial will be stopped if the Data Safety Monitoring Board (DSMB) believes there is an unacceptable risk of serious adverse events in one or more of the treatment arms. No interim analyses of efficacy are planned to there are no formal stopping rules for efficacy or futility.

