## Statistical issues

### Sample size and the detectable difference

The sample size was selected to have adequate power to detect a clinically significant difference of 2.0 points between groups on the Roland Disability scale. Our target sample size of 640 randomized individuals (160 per group) was computed using assumptions described below. Assuming 10% loss to follow-up for each group, there will be outcome data for 144 participants per group. The power of the overall analysis depends on how the four means are distributed. We used the pilot data to estimate the distribution of the means for the four groups and then computed an effect size that was used in the omnibus power calculation.

In the proposed analysis we will first determine if there is an overall difference among the four treatment groups using a two-sided significance level of 0.05. With 144 per group, this omnibus F-test will have 99% power for detecting a statistically significant difference among the four treatment means given the effect size obtained in the pilot study. If this omnibus test is statistically significant, we will compare specified pairs of means as indicated in the proposal. Because this will involve multiple post-hoc comparisons, we will use the Tukey-Kramer multiple comparisons procedure [36] to allow for all possible pairwise comparisons holding the overall α = 0.05. We will not consider a pairwise difference between the means to be statistically significant unless the t-value exceeds 2.61, instead of the usual 1.96.

Both primary outcomes (Roland Disability Questionnaire and bothersomeness of low back pain) are tested at the 0.05 level because they address separate scientific questions. The analyses of covariance of the 8-week pilot data provided estimates of the standard deviations of the primary outcome measures adjusted for pre-randomization baseline values: Roland SD = 4.71 and Bothersomeness SD = 2.73. Using these assumptions, the power to detect a pairwise difference of 2.0 Roland units is 84%, adjusted for multiple comparisons. For the bothersomeness outcome, for which a difference of 1.5 points is considered minimally clinically significant, we will have 98% power to detect a difference of this magnitude. Thus, if our assumptions are correct, 160 participants per group will provide adequate power to detect the smallest clinically meaningful differences on both of our primary outcome measures even after adjustment for multiple pairwise comparisons.

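### The only stated route to serious harms is asking participants, up to 11 times in each acupuncture arm but once in usual care, while hospitalization records already drawn are not used for safety

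*Protocol article*

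**What the plan says.** Four parts of the protocol article bear on this.

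- **How harms are found.** Under Adverse events: "Participants will be asked about adverse experiences at each clinic visit and during the 8-week telephone interviews". Table 3 lists adverse experiences at the 8-week interview and at no other interview. An adverse experience is one "temporally associated with the use of the acupuncture treatments, which could reasonably be related to the procedure". Events first appearing "more than two weeks after a participant's final acupuncture treatment (or more than 9 weeks after randomization for the usual care control group") are not reported.
- **What must be escalated.** The same section sets out which events go to the DSMB without delay: "Any adverse event that is life-threatening or results in death, hospitalization, a persistent or significant disability/incapacity, a congenital anomaly/birth defect, or cancer will be promptly" (the sentence ends by naming the DSMB as recipient). Under Stopping rules, the trial stops if the DSMB "believes there is an unacceptable risk of serious adverse events in one or more of the treatment arms".
- **What the records hold.** Under Measures of health care resource use: "The automated utilization data provide complete information about all provider visits and hospitalizations at health plan facilities or paid for by the health plan". The stated uses are back-pain care, picked out by diagnosis, and the costs of that care. The article does not link these data to safety.
- **How often participants are seen.** The Overview schedules acupuncture visits as "two treatments per week for 3 weeks, weekly treatments for 4 weeks". Usual care has no study visits. The sample-size section plans on this basis: "Assuming 10% loss to follow-up for each group".

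**The concern.** Asking the participant cannot register a death. It can miss a hospitalization when the person is still an inpatient, has dropped out, or is admitted after the last contact. These are among the events that the DSMB most needs to see.

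The chance of being asked also differs by arm. The three acupuncture arms share one schedule, so comparisons among them are not affected by it. Comparison with usual care is. An excess of reported events under acupuncture could reflect more chances to report, and a low count in usual care could reflect fewer. Meanwhile the trial draws on records that do not depend on attendance, recall or arm, but filters them to back-pain diagnoses. An admission for a complication coded under another diagnosis would not be picked up from those records, although they hold it. It would then reach the safety data, by the stated route, only if the participant reported it.

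**Working it through.** **Inputs.** 160 randomized per arm and 10% loss (sample-size section); the visit schedule (Overview); the enquiry points and reporting window (Adverse events, Table 3).

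**1. The plan's own figure.** 160 × (1 − 0.10) = 144 per group with outcome data, as the article states. That leaves 160 − 144 = 16 per arm, and 4 × 16 = 64 in all, without an 8-week interview.

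**2. Scheduled enquiries per participant.**
- Acupuncture arms: 2 × 3 + 1 × 4 = 10 visits, plus 1 interview = 11.
- Usual care: 0 visits, plus 1 interview = 1.

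So the 16 without an interview in usual care are never asked. In the acupuncture arms they may have been asked at up to 10 visits.

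**3. Enquiries against the window.** With a full course the window closes at 7 + 2 = 9 weeks; in usual care it also closes at 9 weeks. The last scheduled enquiry is at week 8. One week of nine (1/9 = 11%) is inside the window with no scheduled question after it.

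**4. Illustration of the share missed.** Assume a constant hazard over nine weeks, loss unrelated to events, the interview held at exactly week 8, and full reporting by everyone asked.
- Usual care: 1 − (144/160) × (8/9) = 1 − 0.80 = 20% missed.
- Acupuncture arms, if everyone lost to the interview still attended all visits to week 7: 1 − [0.90 × (8/9) + 0.10 × (7/9)] = 1 − 0.878 = 12% missed.
- Acupuncture arms, if those lost attended no visits and the same nine-week window is applied: 20%, as in usual care.

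On these assumptions the arms differ by between 0 and about 8 percentage points in the share missed. Loss caused by the event itself would raise the missed share.

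**5. Absolute numbers.** The documents give no hospitalization rate. At assumed rates of 0.5% to 3% over nine weeks, 160 usual-care participants would have 0.8 to 4.8 admissions. Asking would miss 20% of these, which is 0.16 to 0.96.

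**The case against.** The strongest reply is that this is a condensed article. It does not say that asking is the sole route, and a duty to report deaths promptly implies that staff learn of them somehow. Follow-up of missed visits, contact with relatives or notice from clinicians may be set out in the full protocol. That stands: a reader might infer that no other surveillance exists, and the text does not support this. What it supports is that no other route is stated.

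Three further inferences should also be resisted.

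- **That hospitalization generally defeats self-report.** A participant who has been discharged can report the admission at a later visit or at the interview. Only death is wholly beyond this route.
- **That all 64 without an interview are lost to safety ascertainment.** This holds for the 16 in usual care. In the other arms earlier visits may have captured events.
- **That an arm's true serious-event rate could be as high as 10%.** This would need all 16 unheard participants to have had an event. It is a logical ceiling and not an estimate. The 10% is a planning allowance for missing outcome data, and nothing ties it to harm.

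The records have limits too. They cover care at, or paid for by, the plans. The article does not say that they hold deaths or that they arrive quickly enough for prompt reporting. Adverse experiences are confined to events plausibly related to the procedure, so admissions would still need a relatedness judgement.

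The reply does not dispose of the point. The article chose to describe both how harms are sought and what the automated data are for, and as described they leave unequal ascertainment that a source already in use could reduce.

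**Conclusion.** The concern holds as a limited design weakness. The only stated route to adverse events is participant enquiry. It offers up to 11 scheduled enquiries in each acupuncture arm against 1 in usual care, leaves about 16 of 160 usual-care participants never asked at the planned loss, and ends about a week before the plan's own window closes. Serious-event comparison with usual care is therefore confounded with frequency of asking, although hospitalization data that do not depend on arm are already drawn for another purpose.

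The 20% missed in usual care rests on the constant-hazard, independent-loss, exact-timing and full-reporting assumptions above. In absolute terms it is less than one expected admission at the assumed rates. The case for change is that few serious events are expected, so one missed event could matter to a by-arm judgement, and that the remedy is modest. Confidence is medium, because the full protocol may name other routes.

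**What to change.** In Measures of health care resource use and in Adverse events, state that:

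- all-cause hospitalizations, and deaths if the plans' data hold them, will be extracted for all four arms by randomized assignment;
- the period is the existing reporting window, to about week 9. Running the extraction to week 52 would depart from the plan's reasoned window and is not needed for this point;
- relatedness will be judged with assignment masked;
- the results will be tabulated by arm for the DSMB, as a supplement to self-report and prompt reporting and not as a replacement for either.

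If the full protocol already provides another route for serious events, a sentence in the article saying so should accompany this.

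The cost is a query wider than the back-pain extract, review of some unrelated admissions, and the new wording. The records may lag, and care outside the plans would remain uncovered. No treatment or stopping criterion changes.

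### Adverse events are defined by relation to acupuncture yet given a usual-care reporting limit, are asked about up to 11 times against once, and are last asked about before the reporting limit closes

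*Protocol article*

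**What the plan says.** All references are to the protocol article.

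- **Collection.** Adverse events: "Participants will be asked about adverse experiences at each clinic visit and during the 8-week telephone interviews". Table 3 marks the adverse-experience item at the 8-week interview only, with no restriction by arm. The next row, on perceptions of acupuncture, is expressly limited to acupoint-stimulation participants.
- **Definition.** Adverse events: the sign, symptom or disease must be "temporally associated with the use of the acupuncture treatments, which could reasonably be related to the procedure".
- **Reporting limit.** The same section excludes events that first appear more than two weeks after the final acupuncture treatment, "or more than 9 weeks after randomization for the usual care control group".
- **Visits.** Overview: the three acupoint arms attend for "two treatments per week for 3 weeks, weekly treatments for 4 weeks". Under d) Usual care, the fourth arm "will continue to receive the medical care they would have received in the absence of the study"; it has no study treatment visits.
- **Timing of the last question.** Primary measures of efficacy/effectiveness places the 8-week follow-up "one week after completion of the 10 acupuncture treatments".
- **Use of the data.** Stopping rules: the DSMB stops the trial if it believes there is "an unacceptable risk of serious adverse events in one or more of the treatment arms". The Adverse events section sends any adverse *event* meeting a seriousness list promptly to the DSMB, whereas the definition is of an adverse *experience*.

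**The concern.** Three features of one short section do not fit together.

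First, the definition depends on exposure to acupuncture, but the reporting rule assumes that usual care, which has no study acupuncture, will contribute events. Read literally, that arm has almost nothing to report.

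Second, the acupoint arms are questioned repeatedly and usual care once, so a count that combines all sources reflects how often people were asked as well as how often events occurred. Both features push the same way: more reports from the acupoint arms and fewer from usual care.

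Third, the limit on what will be reported closes after the last scheduled question.

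At stake is any safety statement that sets acupuncture against usual care, and the clarity of what the DSMB receives from each arm. The primary outcomes and their analysis are not involved.

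**Working it through.** **1. Reproduce the stated 9-week limit.** Inputs are the visit schedule (Overview) and the two-week rule (Adverse events).

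- Treatments: 2 × 3 + 1 × 4 = 10.
- Length of the course: 3 + 4 = 7 weeks.
- Limit for the acupoint arms on schedule: 7 + 2 = week 9, which matches the 9 weeks stated for usual care.

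**2. Number of solicitations.** Questions = study treatment visits + 8-week interview.

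- Each acupoint arm: 10 + 1 = 11, a maximum that missed visits reduce.
- Usual care: 0 + 1 = 1.
- The individualized, standardized and simulated arms have the same schedule, so contrasts among them are balanced.

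**3. What unequal asking could do (illustration only).** Assume the same underlying risk in both groups and an independent chance p that any one question yields a report. The chance of at least one report is 1 − (1 − p)^11 with 11 questions and p with one.

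| Assumed p | 11 questions | 1 question | Ratio |
|---|---|---|---|
| 5% | 43% | 5% | 8.6 |
| 10% | 69% | 10% | 6.9 |
| 20% | 91% | 20% | 4.6 |
| 30% | 98% | 30% | 3.3 |

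The article gives no reporting probability, and independence between questions is a simplification. The table shows the direction and that the effect need not be small; it is not an estimate for this trial.

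**4. Gap between the last question and the limit.** Let L be the week of the final treatment. The limit closes at L + 2. Because clinic visits also ask, the last question comes at week 8 or week L, whichever is later.

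- L = 7 (on schedule): 9 − 8 = 1 week.
- L = 8: 10 − 8 = 2 weeks.
- L = 9: 11 − 9 = 2 weeks.

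The gap is one week on schedule and at most two if the course runs late. This takes the interview to fall at week 8; a later interview narrows it. For usual care the gap is 9 − 8 = 1 week, counted from randomization and not from a last treatment.

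**5. Definition against limit.** A usual-care event satisfies the definition only if the participant obtained acupuncture outside the study, which the section on health care resource use records as utilization. A separate usual-care limit makes little sense if that were the only route, so the authors evidently meant to report usual-care events. The definition does not let them do so as worded.

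**The case against.** The best defence is that the article proposes no formal comparison of adverse-event rates with usual care: adverse experiences are not among the listed secondary outcomes. Questions at treatment visits exist to detect procedural harm, and an arm without treatment visits cannot be asked at them. The simulated arm has equal ascertainment, and Table 3 already provides a common 8-week item for all four arms. All of this stands, and it limits the point to combined rates set against usual care. It does not remove the conflict between the definition and the usual-care limit.

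Three stronger readings are tempting, and the article does not support them.

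- *Serious events are filtered by relatedness before they reach the DSMB.* A reader might infer this from the definition, but the DSMB sentence refers to any adverse event, and its list includes cancer and congenital anomaly, which sit awkwardly with a procedure-related filter. The two terms leave the matter ambiguous and establish no filter. A full protocol may settle it.
- *Events in the second week after treatment are never recorded, so half the window is lost.* The two-week rule caps what is reported and does not promise questioning up to that date. Half of the calendar time on schedule is not half of the events, and interviews need not fall exactly at week 8.
- *A late course widens the gap without limit.* It does not, because visits after week 8 still ask; two weeks is the maximum.

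**Conclusion.** The concern holds in a bounded form. The Adverse events section contradicts itself on usual care: the definition requires a link to acupuncture, and the reporting limit presumes events in an arm without it. Solicitation is up to 11 against 1, so adverse-event rates that pool visit and interview reports would not be comparable with usual care. Comparisons among the three acupoint arms are sound on this score. The last scheduled question precedes the reporting limit by one week on schedule and by no more than two.

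The counts assume full attendance, and the gap assumes an interview at week 8. The size of any distortion in rates cannot be derived from the article. The point bears on safety reporting against usual care and is worth correcting because correction is cheap; it has no bearing on the efficacy conclusions.

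**What to change.** 1. Define adverse events identically in all four arms without requiring a relation to acupuncture, and record judged relatedness as an attribute of each event.
2. Base any comparison with usual care on the 8-week interview item already scheduled for every arm. Show clinic-visit reports separately, for the three acupoint arms only.
3. Reconcile the reporting window with the collection schedule, for example by ending the between-arm reporting period at the 8-week interview. Adding the item to the 26-week interview is a weaker choice, since an event in week 9 would be recalled after 26 − 9 = 17 weeks.
4. State explicitly that serious events go to the DSMB regardless of judged relatedness, and use one term throughout.

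The cost is reworded definitions, slightly more event reports to process, and a between-arm comparison window that is shorter by about one week on schedule. No visit, treatment or sample size changes.
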